### Recruitment and Enrollment Procedures

Youth presenting at either clinic will be screened by the clinic staff for eligibility and, if applicable, referred to research staff for informed consent. After providing verbal consent, the research staff will determine eligibility. Screening, enrollment, and baseline assessment will occur on the same day whenever possible; otherwise, they will be completed within 1 week. After written consent, participants will be asked to provide a phone number or email and contact information for a family member and/or friend in case they cannot be reached.

### Data Collection Procedures

Table 2 summarizes the study measures, including primary and secondary or exploratory outcomes. Self-report measures will be administered using cloud-based computer-assisted self-interviewing at baseline and 3- and 6-month follow-up. Blood samples for dried blood spot (DBS) testing for HIV viral load will be collected at baseline and 3 and 6 months. Sexually transmitted infection outcomes, including syphilis, gonorrhea, and chlamydia, will be assessed at baseline and 6 months. In computer-assisted self-interviewing, participants view each question and response options on a private iPad (Apple Inc) screen and enter responses directly into password-protected Qualtrics (Qualtrics).

**Table 2 table2:** Study measures.

Measures		Scale or description
**Primary outcomes**		
	Acceptability	System Usability Scale, Client Satisfaction Questionnaire, and exit interviews
	Feasibility	Retention rate ≥85% at 6-month follow-up, number of responses to SMS text messages, and number of HC^a^ sessions completed
	ART^b^ adherence	Visual analog scale, 4-week percent of doses taken, and DBS^c^ for HIV viral load (viral suppression defined as <200 copies/mL)
	Substance use	ASSIST^d^ and AUDIT-C^e^
**Secondary outcomes**		
	IMB^f^ constructs-information	Knowledge of HIV transmission risk and ART knowledge
	IMB constructs-motivation	Behavioral intentions and attitudes toward risk behaviors
	IMB constructs-behavioral skills	Perceived efficacy as a proxy measure of behavior skills
	STI^g^	Syphilis, gonorrhea, and chlamydia
	Sexual risk	Timeline followback: sexual behaviors in the past 30 days
**Secondary and exploratory—contextual factors**		
	Mental health	Brief Symptom Inventory
	Social support	Social Provision Scale
	HIV stigma	Shortened version of the Berger Stigma Scale

^a^HC: Healthy Choices.

^b^ART: antiretroviral therapy.

^c^DBS: dried blood spot.

^d^ASSIST: Alcohol, Smoking, and Substance Involvement Screening Test.

^e^AUDIT-C: Alcohol Use Disorders Identification Test–Consumption.

^f^IMB: information-motivation-behavioral skills.

^g^STI: sexually transmitted infection.

The primary acceptability outcome will be measured by the System Usability Scale, a 10-item Likert scale assessing usability. A score of >70 indicates that technology-based interventions are acceptable [51]. We will also assess interest in future use of the intervention at study completion. For feasibility, we will assess responses to MTM, number of mHC sessions completed, cumulative time spent in mHC, and recruitment rates. Preliminary efficacy outcomes include ART adherence and alcohol use. ART adherence will be measured using (1) the Young Adult Adherence Interview with a visual analog scale [52], (2) 4-week percent of doses taken, and (3) DBS biological testing. Results of DBS testing will be triangulated with self-reports. We will assess integrated behavior model constructs, including knowledge, attitudes, motivations, and behavioral skills related to taking ART, and important contextual factors (depression and HIV stigma).

### Data Analysis

We will estimate retention rates overall and per condition and examine differences across conditions using chi-square tests. We will assess differences in acceptability using 2-tailed *t* tests or Mann-Whitney *U* tests. Minimum criteria for acceptability and feasibility will include a mean System Usability Scale score ≥70 and at least 50% of participants responding to MTM at least once and completing at least 2 mHC sessions [51].

To test the main effects and interactions between components using data from the 2×2 factorial study design, we will use ANOVA with effect coding (−1=“no” condition; +1=“yes” condition) rather than dummy coding. The preliminary intervention effects on ART adherence and substance use outcomes will be assessed using linear mixed-effects models, while viral suppression will be analyzed using mixed-effects logistic regression models. Models will adjust for baseline values of the outcome and relevant covariates and will account for repeated assessments over time. Missing data will be handled using full information maximum likelihood estimation. Effect sizes will be estimated for the primary outcomes.

We will make a preliminary selection of components that have achieved main effects. This selection will then be re-evaluated considering any substantial interaction effects to understand how the components work in combination. Depending on the optimization criterion (viral suppression), this will be combined with other information (eg, cost, feasibility, and scalability) to make a final selection of components. This information will inform the development of an optimized intervention package.

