#### Phase 3: Pilot MOST Design–Based Trial

##### Overview

We will evaluate the feasibility, acceptability, and preliminary efficacy of adapted intervention components to improve HIV self-management and substance use in a MOST design–based trial (ClinicalTrials.gov NCT06415357). The design is shown in Table 1. The trial will examine the effect of each component and whether the presence or absence of a component has an impact on the performance of other components. An advantage of the MOST framework is its ability to identify intervention components that make significant contributions to overall effectiveness and should therefore be retained in an optimized intervention package. We will use a full factorial design because of its relative simplicity and cost-efficiency [46]. For our trial, there are 2 components, each with 2 levels, resulting in a 2×2 full factorial design with 4 experimental conditions (Table 1). We will use viral suppression as a measure of success (viral load <200 copies/mL) [47] and optimization criterion. We will enroll 100 young people with HIV who are not adherent to ART and report unhealthy alcohol use [48] or any drug use. “Standard ART counseling” will be provided to all participants as a constant component. Young people with HIV will be randomly assigned to 1 of 4 conditions (Table 1). The primary outcome will be ART adherence and HIV viral load. The main effects of the components and interactions between them will be estimated using ANOVA. The goal of this pilot trial is to estimate preliminary effect sizes, evaluate feasibility and acceptability, and identify promising intervention components for inclusion in a future fully powered RCT. This protocol is developed in accordance with the SPIRIT (Standard Protocol Items: Recommendations for Interventional Trials) guidelines (Multimedia Appendix 1).

**Table 1 table1:** Full factorial design with 4 experimental conditions.

Experiment conditions	Standard antiretroviral therapy counseling	Mobile Healthy Choices	Motivational text messaging
1 (n=25)	Yes	Yes	Yes
2 (n=25)	Yes	Yes	No
3 (n=25)	Yes	No	Yes
4 (n=25)	Yes	No	No

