### Sample Size of the Trial

This pilot MOST design–based trial is designed to estimate main effects of mHC and MTM and their interaction using a 2×2 factorial study design. Using G*Power 3.1.9 (ANOVA procedure), with effect size f=0.35, α=.05, and sample size=100 (25 per condition), statistical power is 80% for detecting main effects of mHC and MTM and 73% for detecting their interaction. Our proposed pilot trial is not an efficacy study, but our sample is large enough to detect a medium to large effect size of mHC and MTM.

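### Retention is compared only across the four conditions, which does not show whether mHC, MTM or their combination affects it; component-level estimates should be added (minor)

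*Protocol article*

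**What the plan says.** On retention, Data Analysis plans: "We will estimate retention rates overall and per condition and examine differences across conditions using chi-square tests". Neither the layout of the table nor the degrees of freedom is given. Table 1 shows what a condition is: 2 components at 2 levels, "resulting in a 2×2 full factorial design with 4 experimental conditions", 25 participants in each.

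The purpose of the design is stated by component. The Phase 3 Overview says: "The trial will examine the effect of each component", and then adds whether one component alters how the other performs. For main effects and interactions, Data Analysis says: "we will use ANOVA with effect coding (−1=“no” condition; +1=“yes” condition) rather than dummy coding". The models described next cover ART adherence, substance use and viral suppression. Retention is not among them.

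Table 2 lists retention under the primary feasibility outcome, with the benchmark "Retention rate ≥85% at 6-month follow-up". The last paragraph of Data Analysis names feasibility among the further information that is weighed with the optimization criterion in the final choice of components. No rule, target difference or power is attached to the retention chi-square test.

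**The concern.** The unit of decision is the component, but the only retention comparison described is between cells. Even a significant four-group result leaves open whether mHC, MTM or receiving both is responsible, so it does not directly serve the selection step. This part of the point depends on no power figure.

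The second part is efficiency. In a balanced 2×2 factorial, every participant contributes to each component contrast (50 vs 50). A four-group test spreads the same information over 3 degrees of freedom. If one component makes participants leave or stay, the four-group test is less likely to show it, and a pilot meant to inform component choice would report the difference less clearly than its data allow.

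**Working it through.** **Planned figure.** The protocol gives no power for the retention comparison. The 80% and 73% under Sample Size of the Trial are for the ANOVA and play no part here.

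**Inputs from the protocol.** 100 participants, 25 per condition, so 50 vs 50 for each component; retention benchmark 85% at 6 months.

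**Assumptions.** Two-sided alpha of .05, which the protocol states only for the ANOVA. The protocol gives no retention differences, so a range is used.

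**Expected losses at 85% retention.** Per condition: 25 × 0.15 = 3.75, below the usual 5. Per component level: 50 × 0.15 = 7.5.

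**Approximate power, one component acting alone.** With p̄ the mean retention and d the difference between component levels, both tests share the noncentrality λ = N(d/2)² / [p̄(1 − p̄)]. For N = 100, p̄ = 0.85 and d = 0.20: λ = 100 × 0.01 / 0.1275 = 7.84. This gives 64% on 3 df and 80% on 1 df. For d = 0.10: λ = 100 × 0.0025 / 0.1275 = 1.96, giving 19% and 29%.

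**Simulated power.** Counts are small, so the Pearson tests were also simulated (binomial, 25 per cell, 200,000 runs), with mean retention 85% and one component acting:

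| Loss at the two levels | Four groups, 3 df | Component, 1 df, alpha .05 | Component, 1 df, alpha .025 |
|---|---|---|---|
| 7% vs 23% | 42% | 65% | 51% |
| 5% vs 25% | 65% | 85% | 75% |
| 10% vs 20% | 17% | 30% | 19% |
| 15% vs 15% (no difference) | 4.3% | 5.5% | 2.3% |

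The unadjusted gains are about 23, 20 and 14 points. With alpha split over two components they are about 8, 10 and 2. Elsewhere the unadjusted gain can be smaller: for losses of 5% vs 35%, power goes from 93% to 99%. A mid-p version of the component test, unadjusted, gives 61%, 82% and 26% in the first three rows.

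**Patterns that favor the four-group test.**

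- Loss of 35% in the combined arm and 15% in the other three: four-group 40%, each component test 24%. By symmetry the 50 vs 50 interaction contrast (both or neither vs exactly one) also has 24%.
- Crossover, with retention 95/75/75/95% for both, mHC only, MTM only and neither: four-group 65%, each component test 5%. The interaction contrast is then a 75% vs 95% comparison of 50 with 50, with 85%.

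**False positives.** With 15% loss everywhere, two unadjusted component tests give at least one significant result in about 11% of trials, against 4.3% for the four-group test.

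**Precision at 85% retention.** The 95% half-width for a component difference is 1.96 × √(2 × 0.1275/50) = 0.14. For two single conditions it is 1.96 × √(2 × 0.1275/25) = 0.20.

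**The case against.** The strongest reply is that nothing here is stated wrongly. The protocol speaks of chi-square tests in the plural and excludes no component contrast. The article is condensed, and follow-up contrasts may sit in an analysis plan that is not shown. The per-condition rates are planned, and in equal cells the component rates follow by averaging. All of this stands, and it is why the point is an addition to the plan.

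Three stronger readings are tempting, and the documents support none of them.

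- *The four-group test costs about 20 points of power in general.* That figure needs one component acting alone and a single unadjusted test aimed at that component. Two components are to be examined, and splitting alpha cuts the gain to about 2 to 10 points. If attrition comes from the burden of receiving both components, the order reverses.
- *A non-significant result would be taken to show that the handling of missing data is safe.* Data Analysis applies full information maximum likelihood unconditionally. No decision rule uses this p-value, and the retention benchmark is a rate, not a difference between conditions.
- *Expected counts below 5 invalidate the chi-square test.* Its simulated size is 4.3%, slightly conservative. The low counts affect the choice of method for the added estimates but do little harm to the planned test.

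**Conclusion.** The point holds as a minor improvement. The retention comparison described is between four cells, while the trial chooses components and lets feasibility inform that choice. Component contrasts answer that question directly, and they narrow the confidence interval from about ±20 to ±14 points at 85% retention.

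The power advantage is conditional. It reaches a little over 20 points when one component acts alone and no adjustment is made, is about 2 to 10 points with alpha split over two components, and turns into a disadvantage when loss sits in the combined arm. The figures assume 25 per cell, two-sided alpha of .05 and retention differences chosen for illustration. That retention should be examined by component follows from the design and does not depend on those choices.

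**What to change.** Keep the overall and per-condition retention rates and the four-group comparison. Add retention estimates for mHC (yes vs no), MTM (yes vs no) and their interaction, with the −1/+1 coding already chosen for the factorial analysis, each with a 95% confidence interval. Because only 3.75 losses per cell are expected at 85% retention, use penalized logistic regression or an exact or mid-p method. Report the two component effects also as differences in percentage points. State that these are estimates and that no single p-value is confirmatory.

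The cost is a few lines in the analysis plan and no new data. The downside is three more contrasts, with the multiplicity shown above if each is read as a test. The four-group comparison should stay because the added contrasts do not replace it when loss is confined to one cell.

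### Read literally, the viral suppression model adjusts only for baseline suppression yes/no, and nothing commits it to the baseline viral load already collected

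*Protocol article*

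**What the plan says.** All references are to the protocol article.

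- **Phase 3 Overview** sets the criterion: "We will use viral suppression as a measure of success (viral load <200 copies/mL"). It also names HIV viral load itself as a primary outcome, next to ART adherence.
- **Data Analysis** gives the model, "viral suppression will be analyzed using mixed-effects logistic regression models", and the baseline adjustment, "Models will adjust for baseline values of the outcome and relevant covariates". The further covariates are not named.
- **Data Collection Procedures** says: "Blood samples for dried blood spot (DBS) testing for HIV viral load will be collected at baseline and 3 and 6 months". A threshold in copies/mL implies that the result is a quantity.
- **Study Sample** requires self-reported adherence below 80% and sets no viral load criterion.

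**The concern.** The baseline value of a yes/no outcome is itself yes/no. Entry requires poor self-reported adherence, so a sizeable share of participants may be unsuppressed at baseline, and all of them take the same value of that covariate. Someone just above 200 copies/mL and someone at 300,000 copies/mL are treated as having the same starting point, although the second is less likely to be suppressed at follow-up.

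Viral suppression is the criterion for choosing components, and each main effect compares about 50 participants with 50. If the quantitative baseline is left out, the test of each component has less power than the collected data allow. A chance imbalance in starting viral load would also be only partly corrected.

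**Working it through.** **1. The plan's own figure.** The only power statement is "with effect size f=0.35, α=.05, and sample size=100 (25 per condition), statistical power is 80% for detecting main effects of mHC and MTM"; the interaction is given as 73%. It is for a continuous ANOVA effect. With noncentrality λ = N·f² = 100 × 0.35² = 12.25 on 1 and 96 degrees of freedom, power is 93.4% for a main effect and the same for the interaction, so the stated figures do not reproduce. That is a separate matter. Neither set of figures describes the suppression model, and nothing below uses them.

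**2. Assumed inputs.** The article gives no baseline suppression rate, follow-up suppression rate or between-visit correlation, so all three are assumptions. Log10 viral load at two visits is taken as bivariate normal. Baseline values below the 200 threshold are set to the threshold.

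**3. Residual variance of follow-up suppression (50% suppressed at follow-up).** Follow-up suppression is regressed on (a) baseline yes/no and (b) baseline yes/no plus log10 viral load, in large simulated samples.

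Further reduction = 1 − (1 − R²b)/(1 − R²a). Equivalent extra participants per 100 = 100 × [(1 − R²a)/(1 − R²b) − 1].

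- Correlation 0.6, 40% suppressed at baseline: R²a = 0.163, R²b = 0.214. Ratio 0.786/0.837 = 0.939, a fall of about 6%, worth about 6.5 participants.
- Correlation 0.6, 30% suppressed: R²a = 0.146, R²b = 0.224. Ratio 0.776/0.854 = 0.909, a fall of about 9%, worth about 10 participants.
- Correlation 0.7, 20% suppressed: R²a = 0.157, R²b = 0.315. Ratio 0.685/0.843 = 0.813, a fall of about 19%.
- Correlation 0.3, 20% to 70% suppressed: a fall of about 3% down to 0.4%.
- 60% or more suppressed at baseline, correlation 0.3 to 0.7: a fall of at most about 2.5%.

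At correlation 0.6 with 30% suppressed at baseline, the baseline-unsuppressed participants in the lowest viral load quarter are suppressed at follow-up in 58% of cases, against 15% in the highest quarter. The yes/no term cannot see that difference.

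**4. Power in a logistic model.** Simulation with 100 participants, one follow-up, no dropout, a component effect of 0.6 SD on latent log viral load, and control suppression at follow-up 10 points above baseline. One main effect is tested by likelihood ratio at 5%, with 2,000 replicates. The standard error of a single power figure near 70% is √(0.7 × 0.3/2000), about 1 point.

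| Correlation | Baseline suppressed | Yes/no only | Plus log viral load |
|---|---|---|---|
| 0.3 | 20% / 40% / 60% | 67.5 / 68.6 / 58.2% | 69.1 / 68.1 / 59.0% |
| 0.5 | 20% / 40% / 60% | 70.2 / 70.4 / 60.8% | 73.4 / 72.5 / 62.8% |
| 0.7 | 20% / 40% / 60% | 74.9 / 75.8 / 63.8% | 82.0 / 81.8 / 70.2% |

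The gain is about 0 points at correlation 0.3, 2 to 3 at 0.5 and 6 to 7 at 0.7. As a sample-size equivalent, 74.9% to 82.0% gives [(1.96 + 0.915)/(1.96 + 0.671)]² = 1.19, or 19% more participants. Type I error, checked at 40% suppressed, was 4.7% to 6.0% for these two models.

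**5. How steps 3 and 4 fit together.** The 2.5% ceiling in step 3 holds only with 50% suppressed at follow-up. In step 4, the row with 60% suppressed at baseline has 70% of controls suppressed at follow-up, and there the gain at correlation 0.7 is still about 6 points. The result therefore depends on the follow-up rate as well as on the other two inputs.

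**The case against.** The strongest reply is that the article never says the suppression model uses a yes/no baseline. The same sentence allows further covariates, and baseline log10 viral load is a natural candidate because viral load is itself named as a primary outcome. The form of a covariate and the handling of values below the assay limit are usually left to the SAP, which is not shown. This largely stands: the most that can be said is that use of the quantitative baseline is not secured. What remains is that the one baseline term the article does fix is, read literally, the weaker one.

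The second reply is that the size depends on favourable assumptions, and that a linear variance calculation at one visit is not the planned repeated-measures logistic model. This also stands. In a logistic model, adjustment changes both the conditional log odds ratio and its standard error, so the gain is in test power and in precision of a risk difference. It is not a smaller standard error for the log odds ratio. Other covariates, such as baseline adherence, could absorb part of it.

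A reader might infer more, which the article does not support:

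- *Baseline viral load is discarded.* The open covariate list does not exclude it.
- *Suppression is the least powered outcome.* No power is given for it, so this is not shown.
- *Allocation ignores viral load.* The balancing factors under Randomization to Conditions are given only as examples.
- *Component choice turns on this model alone.* Data Analysis also weighs cost, feasibility and scalability, and the sample size section says that the pilot is not an efficacy study.

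**Conclusion.** The point holds as a modest, free improvement. Adjusting for the baseline value of the modelled outcome is valid and conventional. It causes no bias and no type I error problem, and the article does not contradict itself here.

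The benefit of adding log10 viral load ranges from negligible (correlation near 0.3, or most participants suppressed at baseline with 50% suppressed at follow-up) to material (correlation near 0.7, few suppressed at baseline). The middle cases are worth roughly 6 to 10 participants in 100. All of this rests on assumed suppression rates and correlations, and on simulations with one follow-up and no dropout. They show relative gain, not the trial's actual power.

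**What to change.** In the SAP, state that the viral suppression model adjusts for baseline log10 viral load, with values below the assay limit set to that limit, together with the baseline suppression indicator. State also that a standardized risk difference will be reported for each component. If the SAP already names this covariate, nothing needs to change.

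The cost is one sentence and one more model term, with no new samples or visits. Phase 3 began in June 2025, so the text should be settled before outcome data are analysed.

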### Ethical Considerations

This protocol was reviewed and approved by the institutional review boards of the University of Massachusetts Chan Medical School in the United States (STUDY00001496) and the University of Zambia (4548-2023).

